**Methods:**

This study is a clinical trial characterized as randomized, double-blind, double-dummy, and positive drug-controlled. A total of 122 patients diagnosed with CHE have been randomized and allocated in a 1:1 ratio into 2 distinct groups, with one receiving the intervention and the other serving as the control. Participants in the intervention group will receive RZZYL granules along with a placebo cream of mometasone furoate, whereas the control group will get mometasone furoate cream in combination with a placebo for RZZYL granule. Both groups will be treated with either the active drug or a placebo for 4 weeks. The primary outcome metrics are the Hand Eczema Severity Index (HECSI) and the Numerical Rating Scales (NRS). Secondary outcome metrics consist of the target lesion area score, the Patient-Oriented Eczema Measure (POEM), the Dermatology Life Quality Index (DLQI), and the Investigator Global Assessment (IGA). The outcomes will be assessed at the start of the study and again at 2 and 4 weeks after the treatment period.

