**Exit criteria**
Patients will be withdrawn from the trial under the following conditions:Protocol noncompliance: Missing one or more scheduled follow-up visits without prior notification or valid justification; failure to complete at least 80% of the required clinical assessments (eg, symptom diaries and laboratory tests).Safety or medical reasons: Development of a new condition (eg, severe infection and pregnancy) requiring intervention that conflicts with the trial; concurrent use of medications outside the prescribed protocol, particularly those affecting the evaluation of the investigational drug’s efficacy or safety.Participant-initiated withdrawal: Voluntary withdrawal via written or verbal request; loss to follow-up (no contact for 14 days or more despite 3 attempted reach-outs via phone or email).Other: Death or investigator-determined necessity to terminate the trial (eg, Grade 3 or higher adverse event).

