### Intervention

Patients will initially dilute the granules (either the moisturizing and anti-itch wash or the placebo wash) in 1500‐2000 mL of hot water during the treatment period. When the medication cools to around 37°C, instruct the patient to fully immerse both hands in the solution for 15 minutes. After this, the medication will be rinsed off. Following the wash, an external cream (either mometasone furoate cream or placebo cream) will be applied to the affected area using the fingertip unit method, where 1 fingertip unit is sufficient to cover the entire hand of an adult (both front and back). The cream will be applied evenly in a thin layer to cover the lesions fully, followed by gentle circular massaging to enhance absorption. This application will occur once daily. Daily care will be administered throughout the day using Xiehe Vitamin E Cream (Product Standard number SuG Cosmetics Network Backup 2019002615). Clinical researchers will distribute medications biweekly to mitigate the risk of early dropout associated with a single 4-week supply. During the week 4 follow-up, both used and unused wash and cream will be collected, and panoramic photographs of the medication bags and tubes (including the participant ID label) will be taken and archived. A follow-up phone check will be conducted for medications that are not returned within 48 hours to confirm usage frequency and document the reasons for nonreturn. The sensitivity analysis will include participants with adherence rates below 80% or exceeding 120%. Furthermore, all medications used in the study will only be distributed after passing quality control testing.

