### Safety Assessment

Safety indicators will be evaluated through the subsequent assessments:

General physical examination: The patient’s general condition and basic vital signs (body temperature, blood pressure, pulse, and heart rate) will be monitored and recorded both prior to and following enrollment. The participants’ health status will be assessed to determine eligibility for the trial and monitor health changes throughout the trial.Laboratory assessments: At allocation and after 4 weeks of treatment, the assessments that will be conducted are blood routine, urine routine, alanine aminotransferase, aspartate aminotransferase, gamma-glutamyl transferase, total bilirubin, direct bilirubin, alkaline phosphatase, creatinine, urea, and electrocardiogram.Evaluation of skin irritation: Skin erythema, blisters, dryness, scaling, pigmentation changes, tightness, and itching will be assessed and documented at allocation and after a 4-week treatment period.

During each visit to the trial, adverse events were recorded in the participant’s pathological report form. If required, all serious adverse events and unanticipated events should be immediately reported to the Guang’anmen Hospital Ethics Committee and relevant authorities. If the injury assessment confirms that the injury caused by the research is related to the trial, the treatment and compensation costs will be borne by Guang’anmen Hospital of the China Academy of Chinese Medical Sciences. If there is a significant change in the research protocol related to the participant or a substantial increase in the related, it will be essential to resecure his informed consent. In addition, a committee will track participant safety and integrity of the study, called the Data and Safety Monitoring Committee (DSMC). The principal investigator will regularly assess all reported adverse events. Based on necessity, the principal investigator may call for a meeting with the research team to evaluate the risks and benefits. Scheduled interim analyses will be performed to monitor the study’s ongoing safety and amend the study protocol if necessary.

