### Quality Control

Prior to the commencement of the trial, all participating researchers will receive standardized training on diagnostic interviews to ensure familiarity with the management process and to clarify the implementation procedures. During the trial, 2 clinical physicians will evaluate CHE. The allocation will be fixed, and migration between groups will not be permitted. The reason for a participant’s withdrawal from the study will be documented if they discontinue treatment.

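### The skin-irritation checklist has only one post-baseline time point, week 4, so local reactions that clear or lead to exit earlier are missing from it

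*Protocol article*

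**What the plan says.** Under Safety Assessment, the skin-irritation evaluation covers erythema, blistering, dryness, scaling, pigment change, tightness and itch. Its timing is explicit: these items "will be assessed and documented at allocation and after a 4-week treatment period". Laboratory tests follow the same two-point schedule.

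Elsewhere the article describes more contact than that:

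- The abstract schedules the outcomes: "The outcomes will be assessed at the start of the study and again at 2 and 4 weeks after the treatment period". Read with the Outcome Measures section, which places all outcome measurements between baseline and the end of treatment, this means weeks 2 and 4 of treatment.
- Under Intervention: "Clinical researchers will distribute medications biweekly".

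Other routes by which a local reaction could be recorded are:

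- Safety Assessment: "During each visit to the trial, adverse events were recorded in the participant’s pathological report form".
- Textbox 1, exit criteria: "Death or investigator-determined necessity to terminate the trial (eg, Grade 3 or higher adverse event" is a ground for leaving, alongside voluntary withdrawal and use of medication outside the protocol.
- Quality Control: "The reason for a participant’s withdrawal from the study will be documented if they discontinue treatment".
- Data Analyses: the Safety Set keeps everyone who took at least one dose.

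**The concern.** The checklist is the only itemised local tolerability measure that the article describes, in a trial whose objective names safety beside efficacy and whose test product is a daily 15-minute hand soak. With one post-baseline reading, it records what is present at week 4 in patients who are still there. Two kinds of reaction drop out of it: those that start and settle within four weeks, and those that lead the patient to leave first. The second kind makes the week-4 readings selective, because staying in the trial depends partly on tolerating the treatment. If week-4 scores are then compared between arms as the tolerability result, the comparison may be distorted.

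**Working it through.** **No plan figure to reproduce.** The article attaches no rate or sample-size argument to the irritation evaluation, so the check sets the schedules side by side and then illustrates what could follow.

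**Step 1: which checklist items are recorded elsewhere at week 2?** As the article describes them, HECSI scores erythema, papules, scales and fissures; the NRS scores itch; and IGA takes redness into account. Three of the seven items (erythema, scaling, itch) therefore have a week-2 counterpart, though as efficacy measures of the eczema. Those three descriptions do not mention the other four (blistering, dryness, pigment change, tightness). POEM's individual questions are not listed.

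**Step 2: patients who leave early.** The Safety Set keeps them in the denominator, but it cannot supply a checklist reading that was not taken. Multiple imputation is described for the Full Analysis Set, not for the Safety Set.

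**Step 3: illustration. Every rate here is an assumption; none is in the documents.** Let p be the true proportion with a local reaction in an arm, r the share of those cases that resolve before week 4, and w the share that withdraw unscored. The proportion seen on the week-4 checklist is

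p(1 − r − w) / (1 − p·w).

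Take p = 20% in arm A and 10% in arm B, with all of arm B's cases still present at week 4:

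| r in A | w in A | Week-4 reading, A | Week-4 reading, B |
|---|---|---|---|
| 0 | 0 | 20.0% | 10.0% |
| 0.25 | 0 | 0.20 × 0.75 = 15.0% | 10.0% |
| 0.50 | 0 | 0.20 × 0.50 = 10.0% | 10.0% |
| 0.25 | 0.25 | 0.10 / 0.95 = 10.5% | 10.0% |
| 0.50 | 0.25 | 0.05 / 0.95 = 5.3% | 10.0% |

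With p = 30% in arm A, the last row becomes 0.075 / 0.925 = 8.1% against 10.0%.

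**Step 4: what the illustration shows.** With w = 0 and p = 20%, a reversal requires 0.20(1 − r) < 0.10, so r > 0.50 in arm A while arm B loses nothing. If half of the cases resolve early in both arms, the reading is 10% against 5%: the order is kept, but the difference shrinks from 10 points to 5. Loss of early reactions from the checklist therefore needs no imbalance between arms, whereas a change of ranking does.

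**The case against.** The strongest reply is that early reactions have other ways into the safety data. Adverse events are recorded at every visit and reviewed by the principal investigator, a monitoring committee follows safety, withdrawal reasons are documented, and nobody who was dosed leaves the Safety Set. If several patients in one arm stopped because of irritation and none did in the other, the withdrawal reasons would show it. This stands, and it limits the point to the checklist.

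A reader might infer more: that early reactions are never recorded at all, that adverse events are only volunteered by patients, or that the more irritating arm will look safer. The documents do not support these readings. The article does not say how adverse events are elicited. A reversal needs early loss that is both large and concentrated in the less tolerated arm, and nothing in the article says this will happen. Nor does the Data Analyses section name the week-4 checklist comparison as the tolerability analysis.

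Two further replies carry some weight. First, this is a condensed article and its timeline figure is not shown, so silence about a checklist at early withdrawal is not evidence that none is planned. The two-point timing, however, is stated in the text and is not silence; a figure listing a week-2 check would conflict with it. Second, erythema, scaling and itch belong to the eczema itself. Taking the worst score at any visit would count disease remaining at week 2 as irritation and penalise the arm that improves more slowly. That is a valid criticism of a worst-score summary, and the fix below avoids it by counting change from baseline.

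**Conclusion.** The point holds for the structured checklist only. As scheduled, local reactions that resolve or lead to exit before week 4 are not captured on it. They may still be recorded as adverse events or withdrawal reasons, but nothing in the article provides for the seven items to be compared between arms for those patients. A comparison of week-4 checklist scores could understate irritation in the less tolerated arm if early resolution or withdrawal is more frequent there.

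The size is unknown. The table's figures rest on assumed incidence, resolution and withdrawal rates, and on arm B losing no cases; they show that the distortion is possible, not that it is likely. The conclusion also takes the week-2 outcome assessment to fall during treatment. If it did not, the two-weekly dispensing contact would remain as an occasion for the checklist.

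**What to change.** - Complete the same seven-item checklist at the week-2 assessment and, where the patient can be seen, at early withdrawal.
- In the Safety Set, summarise by arm the proportion of patients with any item new or worsened from baseline at any post-baseline assessment. Count a withdrawal for a local reaction as an event.
- Report the checklist by visit as well, next to the adverse-event table, so that all routes of capture are read together.

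The Results section reports 40 of 122 patients recruited by July 1, 2025, which left 122 − 40 = 82 still to enter at that date. If the change comes during recruitment, state when it took effect and show results separately for patients enrolled before and after it, since the earlier ones had fewer chances to be scored.

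The cost is a few minutes per visit, one added case report form page and one extra line in the safety summary. No treatment or stopping rule changes. Reported irritation rates are likely to rise in both arms, and some overlap between irritation items and the eczema itself will remain even with change from baseline.

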### Oversight and Monitoring

### Data Collection and Management

Original documents will be prepared for each participant randomly assigned to the study by the researchers. All pertinent information will be documented in the case report forms and archived in Microsoft Excel spreadsheets. Under the direction of the principal investigator, an internal data monitoring team will oversee and audit the clinical data to maintain data integrity and quality. The case report forms will be reviewed regularly or intermittently, and timely feedback will be provided to the researchers if any issues are identified. All participant data will be maintained strictly confidential and not accessible to the public.

### Data Analyses

The results of this trial will be analyzed from three perspectives:

Full Analysis Set (Intention-to-Treat Analysis): This set includes all randomized participants, with data analyzed according to the principle of “randomization equals analysis.” Missing data will be addressed using multiple imputation methods. Predictive mean matching will be used for continuous variables while logistic regression imputation will be used for categorical variables.Per Protocol Set: This set comprises participants who meet specific criteria; that is, they must have completed at least 80% of the treatment regimen (ie, a minimum of 22 days of medication within 4 weeks), have not used prohibited study drugs, and possess complete data for the primary end point (HECSI score).Safety Set: This set includes all participants who received at least 1 dose of the study medication.

The variable processing and statistical methods for this trial are outlined as follows: (1) continuous variable data that adhere to a normal distribution will be presented as mean (SD). Independent sample *t* tests (2-tailed approach) will facilitate between-group comparisons while repeated measures ANOVA will be applied for comparisons across multiple time points (eg, baseline, during treatment, and post treatment); (2) data that do not conform to a normal distribution will be expressed as median (IQR), with between-group comparisons executed using the Mann-Whitney *U* test; (3) categorical data will be described in terms of proportions or percentages, with between-group comparisons conducted using chi-square tests or Fisher exact test, depending on the final sample size. (4) All data processing and chart generation will be performed using R 4.0 software (R Project for Statistical Computing). Statistical tests will be 2-sided, with a significance level at *P*<.05.

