### Sample Size

This trial aims to objectively assess the efficacy and safety of RZZYL for CHE through a high-quality clinical study design, thereby providing substantial data support for medication development and translation. The trial uses mometasone furoate cream as the positive drug control, categorizing it as a noninferiority trial. According to pertinent literature, the efficacy rate of mometasone furoate cream for treating HE, as assessed by the symptom improvement index using the Nimodipine method, is 53% [21]. Based on previous clinical observations, the efficacy rate for the RZZYL (granules) group is 73.47% [22]. Using the noninferiority study formula (equation 1) [23], with a statistical power (1-β) set at .9, an alpha level (α) of .025, and a noninferiority margin (δ) of 0.095 [24], the values for z_α_ and z_β_ are 1.95996 and 1.28155, respectively, with k (prespecified noninferiority margin) set to 1. The symbol “z” typically represents the critical value in a standard normal distribution, used to calculate the critical region in hypothesis testing. The sample size calculation indicates that the control group requires approximately 53 participants (n_c_). Consequently, the sample size for the experimental group (n_t_) is calculated as k×n_c_=53 participants, leading to a total sample size of 106 participants. Considering an anticipated attrition rate of 15.0% [25], the necessary sample size is adjusted to 61 participants for both the control and experimental groups, resulting in a total required sample size of 122 participants.

(1)
$$n_{c}=\frac{\left(Z_{1-\alpha }+Z_{1-\beta }{)}^{2}\cdot [P_{C}(1-P_{C})+P_{T}(1-P_{T})\right]}{(P_{C}-P_{T}-\delta {)}^{2}}$$

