**Exclusion criteria**
Individuals meeting any of the following criteria will be excluded from participationPresence of any systemic or active skin disorders (eg, psoriasis) or conditions that could affect the evaluation of skin lesions, such as scars, tattoos, birthmarks, or other pigmentary skin conditions.Existence of specific bacterial, viral, or fungal infections at the site of application that require antibiotic therapy.The presence of serious concomitant primary diseases impacting the heart, cerebrovascular system, liver, kidneys, or hematological system, along with individuals experiencing mental health issues.Use of systemic corticosteroids or immunosuppressants within the 30 days leading up to treatment; administration of biologics or small molecule medications within the preceding 90 days; or application of topical corticosteroids or retinoids within a week prior to treatment.Confirmed allergies to any component of the investigational drug.Pregnant or breastfeeding individuals, as well as those planning to conceive in the next 3 months.Participation in other clinical trials for pharmaceuticals in the last 3 months.

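### The Per Protocol Set does not require that patients met the entry criteria, so a patient randomised in breach of most of them stays in both efficacy sets (minor)

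*Protocol article*

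**What the plan says.** Under Data Analyses, the Full Analysis Set takes every randomised participant as randomised. The Per Protocol Set is then defined: "This set comprises participants who meet specific criteria; that is, they must have completed at least 80% of the treatment regimen". The sentence goes on to require that they "have not used prohibited study drugs, and possess complete data for the primary end point (HECSI score"). These are three conditions: exposure, no prohibited drugs, and complete HECSI.

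Sample Size describes the trial by "categorizing it as a noninferiority trial", with a margin of 0.095 and planning response rates of 53% (mometasone) and 73.47% (RZZYL).

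The entry criteria are in Textbox 1. They include HECSI of 27 or less, a specified TCM pattern, age 18 to 70, no other active skin disease, no infection needing antibiotics, and no biologic or small-molecule drug in the preceding 90 days.

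**The concern.** The article gives an explicit definition of the Per Protocol Set, introduced as the meaning of meeting specific criteria, and eligibility is not part of it. This is a stated rule that is too loose, not a detail left to a document we cannot see.

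A per-protocol analysis is normally reported beside the all-randomised analysis in a noninferiority trial, so that a reader can see whether the conclusion also holds in patients who followed and fitted the protocol. The Full Analysis Set properly keeps ineligible patients. If the Per Protocol Set keeps them too, no analysis shows the result without them. If such patients show less difference between the arms, both estimates are pulled towards zero.

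**Working it through.** **Does any other rule remove an ineligible patient from the Per Protocol Set?**

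| Entry breach found after randomisation | Caught elsewhere? |
|---|---|
| HECSI above 27, wrong TCM pattern, age, another active skin disease | No. None of the three conditions mentions them, and the exit criteria do not name them. |
| Systemic corticosteroid, immunosuppressant, biologic or small molecule within 30 days | Yes, if the prohibited-drug condition is read with Concomitant Treatments and Forbidden Drugs, where the restriction starts 30 days before consent or randomisation. |
| Biologic or small molecule 31 to 90 days before | No. It breaches the 90-day exclusion but falls outside the 30-day restriction. |
| Infection needing antibiotics | Probably, if it is treated, because additional treatments are barred. |

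The exit criteria cover noncompliance, a new condition, outside medication, withdrawal and loss to follow-up, death, and termination the investigator judges necessary. The last could be applied to an ineligible patient, but it is discretionary and does not define the analysis set.

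**The plan's own figure.** The inputs from Sample Size are control rate 0.53, RZZYL rate 0.7347, margin 0.095, z values 1.95996 and 1.28155. Equation 1 gives

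n = (1.95996 + 1.28155)² × (0.53×0.47 + 0.7347×0.2653) / (0.53 − 0.7347 − 0.095)² = 10.507 × 0.4440 / 0.08982 = 51.9.

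That is 52 per arm against the stated approximate 53, which is close enough to use 53 below.

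**Model.** A share f of the set has no treatment difference and the rest have the full difference. The test is the noninferiority comparison of two proportions behind the sample size, with unpooled variance. The share f is assumed.

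*Case 1: the true difference in eligible patients is −0.095, at the margin.* The apparent RZZYL rate is 0.53 − 0.095(1 − f), and the one-sided error is P(Z > 1.96 − 0.095f/SE).

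- f = 0: rate 0.435, SE = √[(0.2491 + 0.2458)/53] = 0.0966; error 0.025.
- f = 0.05: rate 0.4398, SE 0.0967, shift 0.00475/0.0967 = 0.049; error 0.028.
- f = 0.10: rate 0.4445, SE 0.0967, shift 0.0095/0.0967 = 0.098; error 0.031.
- f = 0.20: rate 0.454, SE 0.0968, shift 0.019/0.0968 = 0.196; error 0.039.

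*Case 2: the planned difference of +0.2047.* The apparent difference is 0.2047(1 − f), and power is Φ[(difference + 0.095)/SE − 1.96].

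- f = 0: 0.2997/0.0915 = 3.274; power 0.906.
- f = 0.05: 0.2895/0.0920 = 3.146; power 0.882.
- f = 0.10: 0.2792/0.0925 = 3.020; power 0.855.
- f = 0.20: 0.2588/0.0933 = 2.773; power 0.792.

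**Excluding these patients instead, under Case 2.** With f = 0.05 the set is 53 × 0.95 = 50.35 per arm, SE = √(0.4440/50.35) = 0.0939, power 0.891. With f = 0.10 it is 47.7 per arm, SE 0.0965, power 0.874. In this model, leaving them out costs less power than keeping them in (0.882 and 0.855).

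**The case against.** **This is an article, and a list of major deviations usually sits in the analysis plan.** That is fair in general. Here, however, the article chose to define the set and worded it as a definition. A later plan that excluded ineligible patients would depart from the published text.

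**Eligibility is checked before randomisation.** Recruitment places the check in the screening phase, Randomization speaks of eligible participants being assigned, and medication records for the past 3 months are reviewed. This stands, and it is why the breach rate should be low. Screening still does not say what happens to a patient found ineligible afterwards.

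**Late laboratory results.** A reader might infer that organ-disease exclusions will be found late, because the tests are listed as "Laboratory assessments: At allocation and after 4 weeks of treatment" while the exclusions include "The presence of serious concomitant primary diseases impacting the heart, cerebrovascular system, liver, kidneys, or hematological system". The article does not establish this. Trial Design puts laboratory tests among the examinations before therapy, Safety Assessment says health status is assessed to determine eligibility, and the timeline figure is not available. Nor would such a patient's eczema necessarily respond alike to both products.

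**Dilution is not assured.** A patient with HECSI above 27 still has hand eczema. A patient with the wrong TCM pattern might do worse on RZZYL, which would count against noninferiority. This stands and limits the size of the claim.

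**Wrong treatment.** A reader might infer that patients who took the other arm's product also stay in the set. The regimen in the first condition naturally means the assigned one, and Quality Control fixes allocation and bars movement between groups. Only a dispensing error would slip through, and nothing in the article suggests one.

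**Conclusion.** The point holds and is minor. The Per Protocol Set as written keeps patients who breached most entry criteria, so neither efficacy set shows the result in patients who met the protocol.

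Two stronger readings are not supported. The first is that the gap always favours a noninferiority claim. That needs RZZYL to be truly worse and the ineligible patients to show less difference; under the plan's own rates the same dilution lowers power. The second is that the set fails a task the protocol gives it. The article assigns the Per Protocol Set no role in the noninferiority conclusion, and Data Analyses describes only two-sided tests at P<.05.

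At an assumed 5% to 10% of patients with no treatment difference, the error at the margin goes from 2.5% to 2.8% to 3.1%, or power goes from 0.91 to 0.88 to 0.86. These figures rest on the assumed share, on zero difference in those patients, on 53 per arm, and on a binary noninferiority test taken from Sample Size.

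**What to change.** Add a fourth condition to the Per Protocol Set in Data Analyses: no major violation of the inclusion or exclusion criteria, judged on facts that describe the patient before randomisation (even if they came to light later) and decided before unblinding. Leave the Full Analysis Set unchanged. Naming receipt of the assigned kit is optional, since it matters only for a dispensing error.

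The cost is one sentence and a slightly smaller Per Protocol Set: at the assumed shares, 0.05 × 53 = 2.65 to 0.10 × 53 = 5.3 patients per arm. The planned sample size does not change. The article defers unblinding until case collection is complete, so the amendment can be made blind if it is made before then. The same exclusions chosen after unblinding would look selective.

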**Inclusion criteria**
Individuals who satisfy the subsequent criteria will be incorporated into the trial:Diagnosis of mild to moderate CHE by the diagnostic criteria established in the Chinese Expert Consensus on the Diagnosis and Treatment of Hand Eczema (2021 Edition) [26] (HECSI score ≤27).Diagnosis of chronic eczema classified as blood deficiency and wind-dry type according to the Expert Consensus on the Diagnosis and Treatment of Eczema in Traditional Chinese Medicine (2021 Edition) [27].Patients aged 18-70 years (inclusive), both male and female.The primary affected region is the hands.Signed clinical informed consent and ability to adhere to the treatment protocol.

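### No baseline-adjusted between-group analysis is specified for the continuous outcomes, and the observed distribution decides which unadjusted test is used

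*Protocol article*

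**What the plan says.** All references are to the protocol article.

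- **Outcomes and visits (Abstract, Methods).** "The primary outcome metrics are the Hand Eczema Severity Index (HECSI) and the Numerical Rating Scales (NRS"), and "The outcomes will be assessed at the start of the study and again at 2 and 4 weeks after the treatment period". I read the visits as baseline, week 2 and week 4 of treatment, because Outcome Measures has everything recorded between baseline and the end of treatment. Baseline scores are therefore collected.
- **Normal branch (Data Analyses).** "continuous variable data that adhere to a normal distribution will be presented as mean (SD"). For the independent-samples t procedure, "tests (2-tailed approach) will facilitate between-group comparisons while repeated measures ANOVA will be applied for comparisons across multiple time points". The ANOVA covers "comparisons across multiple time points (eg, baseline, during treatment, and post treatment"), so baseline is one of its time levels.
- **Non-normal branch (Data Analyses).** "data that do not conform to a normal distribution will be expressed as median (IQR), with between-group comparisons executed using the Mann-Whitney" procedure. No repeated-measures method is named for this branch.
- **Entry range (Inclusion criteria).** "HECSI score ≤27", which spans the mild (0 to 11) and moderate (12 to 27) bands given under Primary Outcomes.

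The section does not say whether the t and Mann-Whitney tests use week 4 scores or changes from baseline, nor how normality will be judged.

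**The concern.** Two things are at stake, and neither is the validity of the randomised comparison.

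**Precision.** HECSI and NRS are measured before treatment, and a patient's starting score usually says something about the later one. Using it as a covariate removes that part of the between-patient variation from the treatment comparison. The stated tests do not do this, and the ANOVA places baseline on the outcome side.

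**A fixed effect measure.** Whether a primary result is a difference in means or a comparison of ranks depends on the shape of the observed data, judged by an unstated criterion. The second branch is a realistic possibility: HECSI cannot go below 0, entry is capped at 27, and scores are expected to fall under treatment.

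**Working it through.** **1. The plan's own figure.** Sample Size uses control and RZZYL rates of 0.53 and 0.7347, a margin of 0.095, one-sided alpha 0.025 and power 0.90:

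(1.95996 + 1.28155)² × (0.53×0.47 + 0.7347×0.2653) / (0.2047 + 0.095)² = 51.94, that is 52 per arm.

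The article states 53, which is close enough. Allowing for attrition, 53 × 1.15 = 60.95 gives its 61 per arm. This calculation rests on an efficacy rate, "as assessed by the symptom improvement index using the Nimodipine method, is 53" per cent for the control cream. It neither assumes nor tests any analysis of continuous scores, so the point below does not contradict a stated power.

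**2. Variance of the treatment difference.** Let ρ be the correlation between baseline and week 4 scores. The article does not give it, so it is assumed. With equal SDs at both visits, in large samples and relative to a t test on week 4 scores:

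- t test on week 4 scores: 1
- t test on changes: 2(1−ρ)
- ANCOVA on baseline: 1−ρ²

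ANCOVA against the change-score test is therefore (1−ρ²)/(2(1−ρ)) = (1+ρ)/2.

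| ρ (assumed) | ANCOVA ÷ week 4 test | ANCOVA ÷ change test | SE cut vs week 4 | SE cut vs change | 106/(1−ρ²) |
|---|---|---|---|---|---|
| 0.2 | 0.96 | 0.60 | 2% | 23% | 110 |
| 0.3 | 0.91 | 0.65 | 5% | 19% | 116 |
| 0.5 | 0.75 | 0.75 | 13% | 13% | 141 |
| 0.6 | 0.64 | 0.80 | 20% | 11% | 166 |

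The last column is the number of evaluable patients that a week 4 t test would need to match ANCOVA in the planned 106. Both ratios are below 1 for every ρ strictly between 0 and 1, so the conclusion does not depend on which score the t test uses.

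**3. What this means for power.** Take an effect that gives the week 4 t test 80% power at 53 per arm, two-sided 0.05: (1.960 + 0.842) × √(2/53) = 0.544 SD. This is an illustration, not a figure from the article. Power is Φ(2.802/√v − 1.960), with v the relative variance from step 2.

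- ρ = 0.3: week 4 test 80%, change 66%, ANCOVA 84%
- ρ = 0.5: 80%, 80%, 90%

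**4. Does the repeated measures ANOVA recover the loss?** No. Its group-by-time contrast from baseline to week 4 is equivalent to a change-score comparison, so the third column applies. Its group main effect averages in the baseline visit, where randomisation makes the expected difference zero, and so is diluted. The ANOVA is also named only for normally distributed data.

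**5. Limit of these ratios.** They compare ANCOVA with t tests. For the Mann-Whitney branch no such ratio follows without the shape of the distribution. The objection there is that the effect measure is left to the data.

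**The case against.** The strongest reply is that unadjusted tests are valid under randomisation, that covariates and normality criteria are often left to a statistical analysis plan that is not shown, and that the gain depends on a correlation nobody has stated. Most of this stands. The HECSI cap at entry may lower that correlation, and at 0.2 the gain over a week 4 test is trivial. But the article does more than stay silent: it names the tests, and a plan that used ANCOVA would replace that text rather than fill it in.

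Four stronger readings are tempting, and the article does not support them:

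- **That the baseline scores are thrown away.** The sentence that names the t tests also puts baseline into the repeated measures ANOVA, and a t test on changes is not ruled out. Baseline is used inefficiently, not discarded.
- **That repeated measures ANOVA drops patients with a missing visit and so conflicts with the Full Analysis Set.** Data Analyses prescribes multiple imputation for that set, with predictive mean matching for continuous variables.
- **That a baseline imbalance in severity is likely.** With 61 per arm the standardised baseline difference has SE √(2/61) = 0.18. The chance of exceeding 0.2 SD in either direction is about 27%, and 0.25 SD about 17%. Imbalance is possible, and it would not invalidate the test.
- **That the Mann-Whitney test is what stands in the way of the noninferiority comparison.** The only margin, 0.095, is on an efficacy-rate scale, so no analysis in score units, adjusted or not, can be held against it. A rank test can also be paired with a Hodges-Lehmann shift estimate and interval, though none is named.

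**Conclusion.** The point holds as a free improvement. The stated plan contains no between-group analysis of HECSI, NRS, POEM or DLQI with baseline as covariate, and it lets the observed distribution pick the test. The cost is efficiency and an effect measure that is not fixed in advance; there is no bias and no inflation of type I error from leaving baseline out.

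The direction of the precision loss is secure for any correlation strictly between 0 and 1 under equal SDs, whether week 4 scores or changes are tested. Its size is not: it rests on the assumed correlation, and the range 0.3 to 0.6 is an assumption rather than something the article supports.

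**What to change.** In Data Analyses, or in the statistical analysis plan before unblinding, prespecify for HECSI and NRS, and likewise for POEM and DLQI:

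- ANCOVA at week 4 with treatment and baseline score, or a mixed model for weeks 2 and 4 with treatment, visit, their interaction and baseline score, so that baseline is a covariate and not an outcome level;
- that the model is fitted to the multiply imputed Full Analysis Set where imputation is used;
- that the adjusted mean difference with its 95% CI is reported whatever a normality check shows;
- that the Mann-Whitney test is kept as a sensitivity analysis, stating whether it uses week 4 scores or changes.

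The cost is wording only. No new data, visits or patients are needed, and the article places unblinding after case collection is complete.
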